### **Clinical and biological surveillance (Tables 1 and 2)**

Clinical surveillance for group A:

- Step 1: D0, D14, D28 and D56.
- Step 2: D0 (D56 of step 1), D28 (84th day of participation) and D56 (112th day of participation)
- Step 3 (change of dose): D0 (D56 of step 2), D14 (126th day of participation), D28 (140th day of participation) and D56 (168th day of participation).

Clinical surveillance for group B:

- Step 2: D0, D14, D28 and D56.
- Step 3 (change of dose): D0 (D56 of step 2), D14 (70th day of participation), D28 (84th day of participation) and D56 (112th day of participation).

Biological surveillance: blood samples on D0, D2, then weekly until the end of this step for kalaemia, blood samples on D0, D14, D28 and then every month for creatinaemia and urine samples on D0 and then every month for creatininuria, blood inogram and proteinuria.

The specimens for the measurement of kalaemia should be taken without a tourniquet.

Monitoring of kalaemia 48 hours after the initiation of treatment (D2) then every 7 days until the end of the study. Consultation with an investigator, in addition to the planned schedule, if necessary (appearance of an adverse event).

The specimens at inclusion, during consultations and at the end of the study will be taken at the Nephrology Service Day Hospital (NSDH) of the CHU, Reims. The specimens for surveillance of kalaemia will be taken at the usual Medical Analysis Laboratory (MAL) used by patient. An agreement will link the investigational centre and the MAL. The result for kalaemia will be faxed to the CRICAM ([contact]), and the investigational physician will be informed of the result on the same day).

Two groups will be distinguished:

- Group A will comprise patients who start the study on the first day of the study; there will be 14 at inclusion
- Group B will consist of patients who start the study directly at step 2; there will be 17 who will be included specifically

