| 
Materials and Methods
 Principal evaluation criterion: Evaluation of the risk of experiencing an adverse event leading to the termination of treatment. These adverse events are: hyperkalaemia <math>\geq 6</math> mmol/L, hyperkalaemia <math>\geq 5.5</math> mmol/L with 2 spoon-measures/day of KAYEXALATE®, acidosis with alkaline reserve <math>\leq 15</math> mmol/L, arterial hypotension with SAP <math>< 100</math> mmHg, acute renal failure defined as an increase in creatininaemia of <math>> 30\%</math>.
 Secondary criteria: Effect of eplerenone on kalaemia, renal function (GFR measured by the clearance of iohexol, proteinuria, urine and plasma concentrations of NGAL, urinary excretion of TGF-<math>\beta 1</math>, collagen IV and MCP-1) and diuretic effect (fractional excretion of sodium, weight, arterial pressure).
 Experimental scheme
 Monocentric phase II study conducted in a similar way to the model of Simon: the study will include 3 steps of 8 weeks during which the dose of eplerenone will be increased from 25 to 50 mg/day.
 Population / patients
 Inclusion criteria: Renal transplant received at least 2 years previously, treated with cyclosporine and with stable renal function between 30 and 50 mL/min/1.73m^2.
 Exclusion criteria: Kalaemia <math>\geq 5</math> mmol/L at inclusion, history of hyperkalaemia <math>\geq 6</math> mmol/L, receiving treatment with a potassium exchange resin, systolic arterial pressure <math>\leq 110</math> mmHg.
 Investigational plan
 3 steps of 8 weeks during which the dose of eplerenone will be increased from 25 to 50 mg/day. Surveillance will be clinical (the first day of each step, then monthly) and biological (specimens on D0 and D2, and then weekly for each step).
 Conduct of study
 A steering committee, consisting of the investigators and methodologists from the CHU, Reims, will be directed by the principal investigator ([name]) in order ensure the smooth progress of the study.
 Timetable
 Start of step 1: September 2011 and prospective inclusions with sequential succession to steps 2 and 3
 End of study: March 2011 depending on the interval between inclusions.
 |

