**4.2. Description of the study methodology****Study scheme (Figure 1)**

The tolerance study will be carried out by adapting the 2-step scheme of Simon (Simon, 1989) initially, and then by carrying out an increase in doses if tolerance is satisfactory.

From the data in the literature, it appears that the frequency of intolerance to treatment is <7% for a dose of 25 mg/day and <10% for a dose of 50 mg/day, which seems acceptable in this population and leads us to envisage a subsequent therapeutic trial. Conversely, its use does not appear possible if the respective frequencies are >15% and 20%, respectively.

In these conditions, for this tolerance study, we proposed a scheme which includes three successive stages combining the plan of Simon in two stages at a dose of 25 mg/day, and then an increase in dose to 50 mg/day with evaluation at a single time (Figure 1).

Under these conditions, the risk of not revealing unacceptable tolerance of eplerenone in this population is <10% and the risk of deciding, if tolerance permits, to not use it is 27%. There is a 60% chance of interrupting the study before the increase in dose if the hypothesis of unfavourable treatment is correct.

The advantages of the study scheme are that it will demonstrate unacceptable toxicity as early as possible and will detect a possible threshold effect between the doses of 25 mg/day and 50 mg/day which will allow the use of the lowest dose possible.

**Step 1:** 14 patients will be included in the first step, at an eplerenone dose of 25 mg/day. This stage will last 8 weeks. If  $\geq 3$  adverse events requiring the termination of treatment occur during these 8 weeks, the study will be stopped and the treatment will be considered to be too poorly tolerated to be used in this population. If <3 adverse events occur, we will proceed to step 2.

**Step 2:** This will consist of the addition of an additional 17 patients. All of the patients (14+17) will be treated with eplerenone at a dose of 25 mg/day for 8 weeks. If >4 adverse events requiring the termination of treatment occur during the 8 weeks, the study will be stopped and the treatment will be considered to be too poorly tolerated to be used in this population. If  $\leq 4$  adverse events occur, we will proceed to step 3.

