**Step 3:** This will consist of an increase in the dose of eplerenone to 50 mg/day in all patients who participated in step 2. The duration of this step will be 8 weeks. If  $\geq 5$  adverse events requiring the termination of treatment occur, the study will be stopped and the treatment will be considered to be too poorly tolerated to be used in this population. If  $\leq 4$  adverse events occur, the tolerance of eplerenone treatment in this population will be considered to be acceptable.

[figure not shown]

**Figure 1. Study scheme** showing the different possibilities

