#### **4.5. Anticipated duration of participation of subjects and description of the chronology and duration of all periods of the study (including follow-up)**

##### **4.5.1 Expected duration of participation of subjects**

The maximum participation of patients taking part in the study in group A will be 3 steps of 8 weeks, thus 24 weeks in total.

The maximum participation of patients taking part in the study in group B will be the 2 final steps of 8 weeks (2 and 3), thus 16 weeks in total.

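### The printed calendar puts the change to 50 mg on each patient's own day 56 of step 2, while the step 2 rule needs the finished 8-week count in all 31 patients; the two agree only if group B starts on a single day

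*Protocol*

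**What the plan says.** **The rule.** Protocol section 4.2 (study scheme) describes three steps. In step 1, "14 patients will be included in the first step, at an eplerenone dose of 25 mg/day", with a stop at 3 or more terminating events. In step 2, 17 patients are added: "All of the patients (14+17) will be treated with eplerenone at a dose of 25 mg/day for 8 weeks". The step 2 rule is "If >4 adverse events requiring the termination of treatment occur during the 8 weeks, the study will be stopped"; with 4 or fewer, the study goes on to step 3. Of step 3 the protocol says "This will consist of an increase in the dose of eplerenone to 50 mg/day in all patients who participated in step 2".

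**The calendar.** The surveillance part of section 4.2 gives "Step 3 (change of dose): D0 (D56 of step 2" for both groups and lists the later step 3 visits by day of participation: 126, 140 and 168 for group A, and 70, 84 and 112 for group B. Counting back, step 3 begins on participation day 112 in group A and day 56 in group B. Tables 1 and 2 give the last day of one step and day 0 of the next a single shared column, with no waiting or decision column.

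**The limits.** Section 4.5.1 says that maximum participation "in group A will be 3 steps of 8 weeks, thus 24 weeks in total", and that group B takes part for 16 weeks.

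**Inclusion.** The synopsis timetable foresees "prospective inclusions with sequential succession to steps 2 and 3" and an end date that depends on the interval between inclusions. Section 4.2 says that group A starts on the first day of the study and that group B starts directly at step 2.

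**The concern.** The go decision at step 2 belongs to the study: it exists only when all 31 patients have completed 8 weeks at 25 mg or had a terminating event. The dose change in the schedule belongs to the patient: it falls on a fixed day of that patient's own participation. If group B patients do not all start together, the patient-level date arrives before the study-level decision, and the protocol does not say what then happens to the patient.

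If the calendar is followed, some patients take 50 mg before the 25 mg count that is meant to condition it. If the rule is followed, the participation days, the shared column in Tables 1 and 2 and the 24- and 16-week maxima are wrong.

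Only the 31-patient count is involved. Moving from step 1 to step 2 changes no dose, because group A simply continues on 25 mg.

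**Working it through.** **1. When calendar and rule agree**

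Let group A start on study day 0 (section 4.2). Group B can enter only after the step 1 count, so from study day 56. Let the last group B patient enter *W* days after that.

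- Group A's scheduled dose change: day 56 + 56 = 112.
- Step 2 count complete: day 56 + *W* + 56 = 112 + *W*.
- Group A's lead over the complete count: (112 + *W*) − 112 = *W* days.

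The lead is zero only for *W* = 0. The protocol gives no accrual rate, so the windows below are assumptions.

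| Group B entry window (assumed) | Group A scheduled for 50 mg | 31-patient count complete | Lead |
|---|---|---|---|
| 0 | day 112 | day 112 | 0 days |
| 2 weeks | day 112 | day 126 | 14 days |
| 4 weeks | day 112 | day 140 | 28 days |
| 8 weeks | day 112 | day 168 | 56 days |

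With an 8-week window, group A's last scheduled step 3 visit (day 168) falls on the day the step 2 count is completed. If group A's entry is also spread, the leads lengthen: with 4 weeks for each group, the first group A patient is up to 56 days ahead.

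**2. The plan's own error rates, reproduced**

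Inputs are acceptable rates of 7% (25 mg) and 10% (50 mg), unacceptable rates of 15% and 20%, and stopping at ≥3/14, then ≥5/31 cumulative, then ≥5/31 at 50 mg (section 4.2). Outcomes are binomial, with one 25 mg outcome per patient. Step 3 is taken as independent with all 31 entering, the reading that returns the stated figures.

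P(reach step 3) = Σ over x = 0, 1, 2 of P(X₁ = x; 14) × P(X₂ ≤ 4 − x; 17)

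- At 15%: 0.1028 × 0.9013 + 0.2539 × 0.7556 + 0.2912 × 0.5198 = 0.4359.
- At 7%: 0.3620 × 0.9949 + 0.3815 × 0.9727 + 0.1867 × 0.8882 = 0.8971.
- P(≤4 of 31) in step 3 is 0.2287 at 20% and 0.8068 at 10%.
- Detecting unacceptable toxicity: 1 − 0.4359 × 0.2287 = 0.9003 (stated 90.0%).
- Stopping wrongly: 1 − 0.8971 × 0.8068 = 0.2762 (stated 27.6%).

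Both are reproduced.

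**3. Which figures depend on the timing**

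On the printed calendar a patient changes dose only after that patient's own 8 weeks of step 2 at 25 mg. Every 25 mg outcome is therefore observed before the dose changes in that patient. The 31-patient count comes out the same, more than 4 events still stops the study, and the final conclusion rests on the same three counts. So 90.0% and 27.6% stand.

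What changes is whether a step 2 stop comes before anyone has taken 50 mg. At a 15% rate:

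- Both counts complete before the dose change: 1 − 0.4359 = 56.4% (stated 60%, which this does not reproduce).
- Only the step 1 count complete: P(≥3 of 14) = 1 − (0.1028 + 0.2539 + 0.2912) = 35.2% (sum from unrounded terms).
- The difference, 56.4 − 35.2 = 21.2 points, is the probability of a stop at step 2. It is 21.2/64.8 = 32.7% of the trials that pass step 1.

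The true value lies between 35.2% and 56.4%, because a fifth event may occur before day 112 and stop the study in time.

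Section 9.3.1.1 gives ≥4 of 14 as the step 1 limit. On that limit the two ends become 14.7% and 51.2%, but the error rates would be 88.8% and 24.6%, not those stated. That discrepancy is a separate matter.

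**The case against.** The best defence has three parts.

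- **Cohort starts.** Section 4.2 says that group A starts on the first day of the study and group B directly at step 2. If each group starts as a block, calendar and rule match exactly. The synopsis line used against this is weak evidence: its end date of March 2011 precedes its own start date of September 2011.
- **No authorisation.** Step 3 is conditional at study level, and section 4.4.1 ties 50 mg to step 3. The schedule can be read as nominal visit days. Figure 1 may add detail but is not available in the text reviewed.
- **Stopping can be immediate.** Only the go decision needs the complete count, and section 9.1 has events examined as they arise.

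The second and third parts stand. A reader might infer that the protocol orders escalation before the count is known; it does not. A reader might also infer that the 90.0% and 27.6% fail because decisions would rest on incomplete counts. The protocol calls for no such decision, and the working shows those figures unchanged.

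The first part removes the conflict only if all 17 group B patients start on one day. Granting group A a common start does not help, since any spread in group B puts group A's day 112 ahead of the last group B day 56. Whatever its typing error, the synopsis expects inclusions separated by intervals. If the schedule is only nominal, the shared day-56/day-0 column and the exact 24- and 16-week maxima still leave no room for a wait.

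**Conclusion.** The point holds as an unreconciled conflict between a study-level dose-increase rule and a patient-level calendar, confined to the 31-patient count. The mismatch equals the group B entry window when group A starts together: 14 or 28 days for an assumed 2 or 4 weeks.

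The statistical effect is limited to the stated 60% chance of interruption before the dose increase. At a 15% rate this is 56.4% if both counts precede the increase, and could fall towards 35.2% if only the step 1 count does. Those figures rest on independent binomial outcomes and the ≥3 of 14 limit of section 4.2. The lower end is a limit, not a forecast.

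This deserves correction before the study runs. Following the printed calendar with any staggered group B entry would expose patients to the higher dose before the safety count that conditions it.

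**What to change.** Reconcile section 4.2 (step 2 rule), section 4.2 (surveillance schedule, Tables 1 and 2) and section 4.5.1, so that they give one answer to whether a patient may start step 3 before the 31-patient count is complete. Which answer is right is a clinical decision for the sponsor and investigators.

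- **If there is a waiting interval:** state how exposure and events in it are counted, add it to Tables 1 and 2, and revise the participation maxima. For example, with group A starting together, group B entering over an assumed 4 weeks and a common step 3 start, group A would need 24 + 4 = 28 weeks and the first group B patient 16 + 4 = 20 weeks. The 4 to 6 months given in the general information would need checking too.
- **If there is none:** restate the probability of stopping before the dose increase in place of 60%, with the assumed entry pattern.

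The cost is protocol wording and a table revision, and possibly a longer study calendar. No change to the sample size or to the 90.0% and 27.6% follows from this point.

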**Table 1. Timetable for clinical and biological follow-up of group A**

|                                                           | Etape 1 |    |    |     |     |     |     |     |     |          | Etape 2 |    |     |     |     |     |     |     |          |    | Etape 3 |     |     |     |     |     |     |     |   |  |
|-----------------------------------------------------------|---------|----|----|-----|-----|-----|-----|-----|-----|----------|---------|----|-----|-----|-----|-----|-----|-----|----------|----|---------|-----|-----|-----|-----|-----|-----|-----|---|--|
|                                                           | J0      | J2 | J7 | J14 | J21 | J28 | J35 | J42 | J49 | J56 = J0 | J2      | J7 | J14 | J21 | J28 | J35 | J42 | J49 | J56 = J0 | J2 | J7      | J14 | J21 | J28 | J35 | J42 | J49 | J56 |   |  |
| Recueil du consentement                            | x       |    |    |     |     |     |     |     |     |          |         |    |     |     |     |     |     |     |          |    |         |     |     |     |     |     |     |     |   |  |
| Clinique                                           |         |    |    |     |     |     |     |     |     |          |         |    |     |     |     |     |     |     |          |    |         |     |     |     |     |     |     |     |   |  |
| Pression Artérielle                                       | x       |    |    | x   |     | x   |     |     |     | x        |         |    |     |     | x   |     |     |     | x        |    |         | x   |     | x   |     |     |     |     | x |  |
| Recherche d'effets indésirables                           | x       |    |    | x   |     | x   |     |     |     | x        |         |    |     |     | x   |     |     |     | x        |    |         | x   |     | x   |     |     |     |     | x |  |
| Poids                                                     | x       |    |    | x   |     | x   |     |     |     | x        |         |    |     |     | x   |     |     |     | x        |    |         | x   |     | x   |     |     |     |     | x |  |
| Electrocardiogramme                                       | x       |    |    |     |     | x   |     |     |     | x        |         |    |     |     | x   |     |     |     | x        |    |         |     |     | x   |     |     |     |     | x |  |
| Biologique                                         |         |    |    |     |     |     |     |     |     |          |         |    |     |     |     |     |     |     |          |    |         |     |     |     |     |     |     |     |   |  |
| Fonction rénale estimée (eDFG par MDRD)                   | x       |    |    | x   |     | x   |     |     |     | x        |         |    |     |     | x   |     |     |     | x        |    |         | x   |     | x   |     |     |     |     | x |  |
| Kaliémie                                                  | x       | x  | x  | x   | x   | x   | x   | x   | x   | x        | x       | x  | x   | x   | x   | x   | x   | x   | x        | x  | x       | x   | x   | x   | x   | x   | x   | x   | x |  |
| Fraction excrétée de sodium (FeNa + )          | x       |    |    |     |     | x   |     |     |     | x        |         |    |     |     | x   |     |     |     | x        |    |         |     |     | x   |     |     |     |     | x |  |
| Ionogramme urinaire (NaU, KU), créatininurie, protéinurie | x       |    |    |     |     | x   |     |     |     | x        |         |    |     |     | x   |     |     |     | x        |    |         |     |     | x   |     |     |     |     | x |  |
| Albuminurie                                               | x       |    |    |     |     |     |     |     |     | x        |         |    |     |     |     |     |     |     | x        |    |         |     |     |     |     |     |     |     | x |  |
| Sérothèque                                                | x       |    |    |     |     |     |     |     |     | x        |         |    |     |     |     |     |     |     | x        |    |         |     |     |     |     |     |     |     | x |  |
| Urinothèque                                               | x       |    |    |     |     |     |     |     |     | x        |         |    |     |     |     |     |     |     | x        |    |         |     |     |     |     |     |     |     | x |  |
| Fonctionnel                                        |         |    |    |     |     |     |     |     |     |          |         |    |     |     |     |     |     |     |          |    |         |     |     |     |     |     |     |     |   |  |
| Echo-doppler de greffon                                   | x       |    |    |     |     |     |     |     |     |          |         |    |     |     |     |     |     |     |          |    |         |     |     |     |     |     |     |     | x |  |

**Table 2.** Timetable for clinical and biological follow-up of group B

|                                                           | Etape 2 |    |    |     |     |     |     |     |     |          | Etape 3 |    |     |     |     |     |     |     |     |  |
|-----------------------------------------------------------|---------|----|----|-----|-----|-----|-----|-----|-----|----------|---------|----|-----|-----|-----|-----|-----|-----|-----|--|
|                                                           | J0      | J2 | J7 | J14 | J21 | J28 | J35 | J42 | J49 | J56 = J0 | J2      | J7 | J14 | J21 | J28 | J35 | J42 | J49 | J56 |  |
| Recueil du consentement                            | x       |    |    |     |     |     |     |     |     |          |         |    |     |     |     |     |     |     |     |  |
| Clinique                                           |         |    |    |     |     |     |     |     |     |          |         |    |     |     |     |     |     |     |     |  |
| Pression Artérielle                                       | x       |    |    | x   |     | x   |     |     |     | x        |         |    | x   |     | x   |     |     |     | x   |  |
| Recherche d'effets indésirables                           | x       |    |    | x   |     | x   |     |     |     | x        |         |    | x   |     | x   |     |     |     | x   |  |
| Poids                                                     | x       |    |    | x   |     | x   |     |     |     | x        |         |    | x   |     | x   |     |     |     | x   |  |
| Electrocardiogramme                                       | x       |    |    |     |     | x   |     |     |     | x        |         |    |     |     | x   |     |     |     | x   |  |
| Biologique                                         |         |    |    |     |     |     |     |     |     |          |         |    |     |     |     |     |     |     |     |  |
| Fonction rénale estimée (eDFG par MDRD)                   | x       |    |    | x   |     | x   |     |     |     | x        |         |    | x   |     | x   |     |     |     | x   |  |
| Kaliémie                                                  | x       | x  | x  | x   | x   | x   | x   | x   | x   | x        | x       | x  | x   | x   | x   | x   | x   | x   | x   |  |
| Fraction excrétée de sodium (FeNa + )          | x       |    |    |     |     | x   |     |     |     | x        |         |    |     |     | x   |     |     |     | x   |  |
| Ionogramme urinaire (NaU, KU), créatininurie, protéinurie | x       |    |    |     |     | x   |     |     |     | x        |         |    |     |     | x   |     |     |     | x   |  |
| Albuminurie                                               | x       |    |    |     |     |     |     |     |     | x        |         |    |     |     |     |     |     |     | x   |  |
| Sérothèque                                                | x       |    |    |     |     |     |     |     |     | x        |         |    |     |     |     |     |     |     | x   |  |
| Urinothèque                                               | x       |    |    |     |     |     |     |     |     | x        |         |    |     |     |     |     |     |     | x   |  |
| Fonctionnel                                        |         |    |    |     |     |     |     |     |     |          |         |    |     |     |     |     |     |     |     |  |
| Echo-doppler de greffon                                   | x       |    |    |     |     |     |     |     |     |          |         |    |     |     |     |     |     |     | x   |  |

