##### **Secondary criteria:**

- use of a potassium exchange resin
- systolic arterial pressure, diastolic, mean
- weight
- renal function (creatininaemia and creatinine clearance calculated using the MDRD formula)
- vascular resistance of the renal transplant
- natraemia, fractional sodium excretion ( $\text{FeNa}^+$ )
- natriuresis, creatininuria, kaluresis
- proteinuria, albuminuria

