### 4.4. Experimental drugs

#### 4.4.1 Description of the dose and methods of administration of the experimental drug(s)

Eplerenone 25 mg/day or 50 mg/day as a single dose by mouth to be taken every day of the study: 25 mg/day during steps 1 and 2, then 50 mg/day during step 3.

This treatment will be provided to the patients by the promoting centre. The pharmacy associated with this study is the pharmacy of the CHU, Reims (Hôpital Robert Debré), and the pharmacist responsible for this study is [name].

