##### **4.6.1 For participation of a patient in the study**

The participation of a patient finishes either at the end of the study (end of step 3) or after the development of an adverse event requiring the premature termination of eplerenone in this patient.

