##### **4.6.2 For all or part of the study**

The end of the study will either be at the end of step 3 or after the development of a large number of adverse events requiring the premature termination of eplerenone in the patients as defined in section 4.2.

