##### **Functional data**

Vascular resistance of the transplant

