## 9. STATISTICS

### 9.1. Description of the statistical methods planned, including the timetable for any intermediate analyses if applicable

#### Global analysis

The analysis of the primary evaluation criterion will be carried out by a detailed breakdown as soon as the development of an adverse event(s) necessitates the termination of eplerenone treatment (see section 4.2). This will be a descriptive analysis.

The analysis of the secondary criteria will be descriptive and comparative between before and under eplerenone treatment.

Discontinuous variables will be expressed as percentages and continuous variables as the mean  $\pm$  standard deviation.

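### The second graft echo-Doppler is tied to the end of the 50 mg step, so a stop at 25 mg leaves graft vascular resistance, a minor secondary criterion, with baseline values only

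*Protocol*

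**What the plan says.** Section 4.1 lists "vascular resistance of the renal transplant" among the secondary criteria. In section 4.9 it is the only item under functional data: "Vascular resistance of the transplant".

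The examination that supplies it appears in Tables 1 and 2 as "Echo-doppler de greffon". Group A has one mark at day 0 of step 1 and one at day 56 of step 3. Group B has one at day 0 of step 2 and one at day 56 of step 3. Neither table has a mark in the columns that close a 25 mg step.

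Section 4.4.1 gives the dose by step: "25 mg/day during steps 1 and 2, then 50 mg/day during step 3". Section 9.1 states: "The analysis of the secondary criteria will be descriptive and comparative between before and under eplerenone treatment".

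Section 4.2 allows the trial to stop after step 1 or step 2, and section 4.6.2 confirms this: "The end of the study will either be at the end of step 3 or after the development of a large number of adverse events" that require treatment to be stopped. Under section 4.6.1 a patient's participation also ends at such an event. No section schedules a Doppler at either kind of exit. The sentence in section 4.2 on samples taken at inclusion, at consultations and at the end of the study concerns specimens, not imaging.

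**The concern.** The second examination depends on a step that may never take place. Stopping at 25 mg is a planned outcome, and section 4.2 itself puts its chance at 60% if tolerance is unfavourable. The baseline Dopplers would then have been done with nothing to compare them with, and no analysis plan can recover an image that was not taken.

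Other measurements are protected against this. Albuminuria and the serum and urine banks are marked at entry and at the end of every step, so they would have an on-treatment value at 25 mg. Among the repeated measurements only the Doppler skips the step boundaries, and the protocol gives no reason.

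What is at stake is one declared criterion, not the conclusion on tolerance.

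**Working it through.** **1. Reading the tables.** In Table 1 the Doppler row has marks in cells 1 and 29. The kalaemia row, marked at every visit, also ends at cell 29, so the second Doppler mark is day 56 of step 3. The one-cell offset from the header comes from text extraction. In Table 2 the marks are in cells 1 and 19, the first and last visits. Dopplers scheduled at 25 mg after entry: none in either group.

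**2. Inputs for the chance of stopping at 25 mg.**
- 14 patients in step 1 and 17 more in step 2 (section 4.2).
- Step 1 stops at 3 or more events in section 4.2, but at 4 or more patients in section 9.3.1.1. The two need to be reconciled; both are computed here.
- Step 2 stops at 5 or more of 31 (both sections).
- Intolerance rates at 25 mg: 7% acceptable, 15% unacceptable. At 50 mg: 10% and 20%.
- Assumption: each patient contributes one event or none to a cumulative count at 25 mg, with a constant and independent risk.

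**3. Formula.** With X1 ~ Bin(14, p), X2 ~ Bin(17, p) and step 1 stopping at r or more:

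P(stop at 25 mg) = P(X1 ≥ r) + Σ P(X1 = x) · P(X2 ≥ 5 − x), summed over x = 0, …, r − 1.

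**4. Case p = 0.15, r = 3.**
- P(X1 = 0, 1, 2) = 0.1028, 0.2539, 0.2912, so P(X1 ≥ 3) = 0.352.
- P(X2 ≥ 5, 4, 3) = 0.0987, 0.2444, 0.4802.
- Step 2 term: 0.0101 + 0.0620 + 0.1399 = 0.212.
- Total: 0.352 + 0.212 = 0.564.

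**5. Check against the plan's own figures.** Treat step 3 as 31 independent patients stopping at 5 or more; the chance of a step 3 stop is then 0.7713 at 20% and 0.1932 at 10%. With r = 3:
- Unfavourable rates: 1 − (1 − 0.5641)(1 − 0.7713) = 0.900. Section 9.3.1.1 states 90.0%.
- Favourable rates: 1 − (1 − 0.1029)(1 − 0.1932) = 0.276. Section 9.3.1.1 states 27.6%.

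Both agree, so the model is the one behind the plan. The 60% in section 4.2 corresponds to 56.4% here, a small difference that does not affect this point.

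**6. All cases.**

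| Step 1 rule | True rate | Stop in step 1 | Stop in step 2 | Stop at 25 mg |
|---|---|---|---|---|
| 3 or more (section 4.2) | 15% | 0.352 | 0.212 | 56.4% |
| 3 or more (section 4.2) | 7% | 0.070 | 0.033 | 10.3% |
| 4 or more (section 9.3) | 15% | 0.147 | 0.366 | 51.2% |
| 4 or more (section 9.3) | 7% | 0.014 | 0.052 | 6.6% |

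**7. Examinations lost.** If the step is fully recruited, 14 baselines are unused after a step 1 stop and 14 + 17 = 31 after a step 2 stop. At 15% with the section 4.2 rule, 0.352/0.564 = 62% of early stops fall in step 1, so 14 is then the commoner loss.

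**8. If the trial runs to the end.** Up to 4 patients may leave at 25 mg without stopping the trial. If step 3 events are counted separately, up to 4 more may leave at 50 mg with tolerance still judged acceptable. So up to 8 of 31 could lack a second Doppler through adverse events alone. Hypotension and a creatinine rise above 30% are among the exit criteria (section 4.1), so those without a value may not resemble those with one.

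**The case against.** **No statement is broken.** Section 9.1 promises a comparison "comparative between before and under eplerenone treatment". Entry against day 56 of step 3 is such a comparison; nothing is promised by dose or after an early stop. This stands: it is a gap in the schedule. A reader might infer that the tables contradict section 9.1, but if step 3 completes they do not.

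**The criterion is peripheral.** Section 3.2 names chiefly eGFR and proteinuria, with weight and sodium excretion. These are measured in every step. Graft resistance appears in no objective and not in the synopsis list. This stands and limits the weight of the point.

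**The primary objective is not touched.** Because section 3.1 speaks of 25 or 50 mg, a reader might infer that the missing 25 mg Doppler weakens the main question. The documents do not support that. The objective is tolerance, and the Doppler plays no part in the stopping rules.

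**Imaging at entry and at maximum exposure is a defensible choice.** Section 12.2 says the effect on renal function takes much longer than this study. That explains a late second examination in completers. It does not explain having none when the trial ends sooner.

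**Moving the examination does not supply a 25 mg value in completers.** This is correct. If the trial completes, any 25 mg values would come only from patients who left early. Setting these against completers at 50 mg would confuse dose with the reason for leaving. An exit examination may also fall after the drug has been stopped, and section 2.1 gives a half-life of 4 to 6 hours.

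**Duration differs between groups (24 and 16 weeks).** This affects every step 3 measurement and is no fault of the Doppler schedule.

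**Conclusion.** The point holds as a cheap improvement to a minor criterion. If the trial stops in step 1 or 2, graft vascular resistance has baseline values only and the section 9.1 comparison cannot be made for it. The chance is 51% to 56% at a true rate of 15% and 7% to 10% at 7%, depending on which step 1 rule applies. These figures rest on independent patients with one constant risk at 25 mg. Patients who leave early are lost to this criterion in any case.

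The tolerance decision is unaffected. If step 3 completes, the baseline to 50 mg comparison stands for the patients who reach it.

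**What to change.** Add a footnote to the Doppler row of Tables 1 and 2. The second planned examination is done at day 56 of step 3 or, if the trial stops earlier, at the closing assessment of the patients still on treatment. For a patient who leaves, it is done at the exit visit where feasible. Record the dose, the time on treatment and the time since the last intake.

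Report each change from baseline descriptively by dose at the examination. State that values from early leavers at 25 mg set against completers at 50 mg are not a dose comparison.

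**Cost.** There are still two examinations per patient at most, with no change to dose, stopping rule or sample size. Some patients who would have had no second examination will now have one. Values will come at mixed doses and durations, and some exit examinations will be taken during an adverse event or just after the drug is stopped. Completers still have no 25 mg value; that would need a third examination at the end of the last 25 mg step, which is not needed to close this gap.
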